### Blinding

Due to the nature of this trial it is not possible to blind the participants. Nevertheless, the diabetes midwives in charge of the random allocated sequence at the centers are not involved in the preparation of the envelopes, the use of web-based support or in the statistical analyses.

### Intervention

#### The web support group - intervention group

All of the women receive the usual care at one of the six study centers in Sweden. Each center has a special program for pregnant women with type 1 diabetes, and what constitutes usual care varies slightly between the care centers. However, all women have frequent contact with a midwife specialized in type 1 diabetes, an obstetrician and an endocrinologist during pregnancy and at one follow-up visit after childbirth.

In order to further support the women’s well-being and diabetes management, the intervention offers complementary web-based, person-centered support [16–18] in addition to usual care.

The web support springs from a holistic approach and consists of three components: 1) evidence-based information divided into three parts - being pregnant, labor and childbirth, and life as a new mother; 2) a self-care diary for self-reported monitoring of blood glucose, insulin doses, diet, activities and daily mood - measures can be viewed and evaluated in tables and diagrams to support decision making and self-care; and 3) a discussion forum for peer support divided into three parts - being pregnant, labor and childbirth, and life as a new mother - moderated by the research group. The website also provides a Frequently Asked Questions section as well as links to other sites that are relevant for childbearing women with type 1 diabetes.

The web-based information for pregnant women and new mothers with type 1 diabetes has been developed with a participatory design in seven different stages. The development process was driven by researchers, but it also engaged health-care professionals such as nurses, midwives, and physicians specializing in diabetes care, pediatrics, obstetrics and breastfeeding [18]. The web prototype containing the elements of the web support was further developed and tested by potential users, pregnant women and mothers with type 1 diabetes [16] before the web support program was launched.

The web-support system is used freely by the participants in the intervention group. There is no requirement regarding time spent logged into the system. If a participant in the intervention group has not accessed the web-based support within the last fortnight, a reminder is sent out via text message. The research group has no way of monitoring and/or limiting access to other web-based forums in relation to diabetes or childbearing during the study period. A minimum of two independent logons to the system is required for the participant to be considered to be adhering to the intervention.

#### Control group

The women in the CG receive the same usual care at one of the six study centers in Sweden (described above) as those in the IG.

### Follow-up period and outcome measurement

During the 18-month follow-up period, the primary and secondary outcomes are tested at baseline, early pregnancy (T0), late pregnancy (T1), two months after childbirth (T2), and six months after childbirth (T3) (see Figure 2). Outcome measures are collected by questionnaires mailed to the participants in IG and CG. Participants who have not returned the questionnaire within ten days receive a phone call from the study coordinator or project assistant as a gentle reminder.

**Figure 2 Fig2:**
[figure not shown]
**Time periods for measurement of primary and secondary outcomes.**

The study coordinator takes responsibility for the collection and entry of data into the correct computer files per protocol. Data collection will not be continued if a subject has been excluded from the study or has opted out. All data entry will be reviewed by two members of the research group who have not entered any of the data. The primary investigator (PI) has responsibility for the final data files and decides who will be granted access and for what purpose. The PI is also responsible for documenting and communicating any modifications in study protocol to all relevant parties. The sponsors and funders of this trial have no influence over any part of the study’s design or reporting of outcomes.

#### Primary outcome measures

The primary outcome of general well-being is evaluated with the Well-Being Questionnaire, short version (W-BQ12) [19] and diabetes empowerment with the Diabetes Empowerment Scale, short version (SWE-DES) [20].

#### Secondary outcomes measures

Coping in daily life is evaluated using the Sense of Coherence 13-item questionnaire (SOC-13 items) [21], and self-rated health will be assessed using a single-item EVGFP: excellent, very good, fair or poor. Diabetes management is measured with the Problem Areas in Diabetes Scale (SWE-PAID-20) [22]. Fear of hypoglycemia is assessed with the Hypoglycemia Fear Survey (SWE-HFS) [23]. The breastfeeding rate and experiences of nursing are evaluated with a specially developed questionnaire. Medical outcomes in terms of a glycated hemoglobin test (HbA1c) measured in early and late pregnancy and up to six months postpartum are collected from electronic medical records. Usefulness and usability of the web support are evaluated with a specially developed questionnaire and the level of participation by using Google Analytics. Socio-demographic variables, mode of delivery, diabetes duration and type of insulin administration are also recorded. All data collection forms listed above can be obtained from the corresponding author upon request.

### Validity and reliability of instruments used

The research group has opted to use well-tested instruments as outcome measures whenever possible. All instruments have to be available in Swedish to be used in this study. In the primary outcome measurements the W-BQ12 has a described Cronbach’s alpha of >0.88 [19] and its validity is considered to be good. The other primary outcome scale, SWE-DES, is considered acceptable in terms of reliability (Cronbach’s alpha range of 0.68 to 0.91 in the 23-question version of the scale) [20, 24]. In terms of secondary outcome, the Sense of Coherence 13-item scale is recognized as a reliable and valid instrument that can be applied across different cultures (range of Cronbach’s alpha 0.70 to 0.92 in 127 studies) [21]. The SWE-PAID-20 questionnaire was reported to have a (Cronbach’s alpha of 0.94) [25]. The SWE-HFS scale has also been reported as having good reliability (Cronbach’s alpha 0.85) and validity [22].

### Safety evaluation

The web-based support is not considered to cause any adverse event. The participants’ pregnancy statuses are monitored in order to avoid sending questionnaires to women who have experienced a lost pregnancy, and dates for delivery are registered to keep the deadlines for follow-up at two and six months post-partum.

### Trial duration

The inclusion period is estimated from November 2011 to December 2014 with follow-up until February 2016. See Table 1 for a time plan of the study and follow-up.

**Table 1 Tab1:** **Time plan of the study and follow-up**

	Started	Will be completed in
Inclusion	November 2011	December 2014
Early pregnancy (T0)	November 2011	December 2014
Late pregnancy (T1)	April 2012	June 2015
Childbirth	June 2012	August 2015
2 months post partum (T2)	August 2012	October 2015
6 months post partum (T3)	November 2012	February 2016

### Statistical analyses plan

The full analysis set, Intention To Treat population (ITT population), consists of all randomized patients who had at least one follow-up measurement. The Per-Protocol population (PP population) consists of all patients in the ITT population without any significant protocol deviations. The PP population is defined at the clean-file meeting before the database is locked. Primary efficacy analyses will be performed on our two primary variables general well-being (W-BQ12) total score and diabetes empowerment (SWE-DES) total score, both at six months after delivery between the two randomized groups using Fisher’s non-parametric permutation test on the full analysis set (ITT population), two-sided test on significance level 0.025. If significant differences in baseline variables are found between the two randomized groups, a complementary analysis of covariance (ANCOVA) will be performed adjusted for these baseline variables. Last observation carry forward (LOCF) will be applied from two months if the six months value is missing.

Statistical analyses will be conducted using SPSS, version 16.0, and SAS, version 9.2 (Cary, NC). All tests will be two-tailed and conducted at 5% significance level.

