### Randomization and allocation concealment

Participants are randomly allocated to the intervention group (IG) with web support with evidence-based information, self-care diary and communication with pregnant women with type 1 diabetes in addition to usual care, or to the control group (CG) provided only the usual care. Randomization is performed before baseline assessment.

The randomization is prepared with a unique code that consists of a first code letter identifying each center, a second code letter identifying which group it belongs to, and intervention (IG) or control (CG) followed by a consecutive number. Baseline questionnaires are marked with unique code letters/numbers and placed in a closed envelope. The envelopes are produced in blocks of ten, five IG and five CG. This is prepared by the research group and includes the single blind number. The allocation of participants will be equal (1:1) in blocks of ten for each of the six centers. After informed consent is received, the responsible diabetes midwife at each center gives the included woman a closed envelope and registers her personal information and the obtained code letters/numbers. The key connecting the code with the woman’s personal information is stored in a safe location at the study center, in accordance with that specific hospital’s policy. All data files used for data analysis contain the code number as the only source of identification.

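### Allocation is blocked within six centres, but the primary permutation test is described without centre; permuting within centre is a free, minor gain in power

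*Protocol article*

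**What the plan says.** Randomization and allocation concealment describes restricted randomisation: "The envelopes are produced in blocks of ten, five IG and five CG", and "The allocation of participants will be equal (1:1) in blocks of ten for each of the six centers". The participant code begins with a letter for the centre, and that code stays in the analysis files.

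The Statistical analyses plan compares W-BQ12 and SWE-DES, "both at six months after delivery between the two randomized groups", with a Fisher "non-parametric permutation test on the full analysis set (ITT population), two-sided test on significance level 0.025". Neither centre nor block is mentioned, and the way labels are permuted is not described. The only adjustment is conditional: if baseline variables differ significantly between the groups, "a complementary analysis of covariance (ANCOVA) will be performed adjusted for these baseline variables".

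On differences between centres, the Intervention section says only that "what constitutes usual care varies slightly between the care centers". No outcome variance by centre is given.

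**The concern.** A permutation test takes its reference distribution from the allocations that could have occurred. Blocking within centre keeps the two groups nearly equal in every centre. A permutation over all women, ignoring centre, also counts allocations in which one centre falls mostly into one group. If outcomes differ between centres, those allocations widen the reference distribution, while the actual design has already removed that source of error from the group difference. The p-value then tends to be too large.

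The conditional ANCOVA does not close the gap. It is triggered by significant baseline differences, and centre, being balanced by design, would hardly ever show one. What is at stake is some power on both primary outcomes.

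**Working it through.** **1. The plan's own figure.** The article states 68 women per group for 80% power at 0.05. With n = 2(z₁ + z₂)²(SD/difference)² and z₁ + z₂ = 1.960 + 0.842 = 2.802:

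- as printed, W-BQ12 (1.25, SD 0.40): 2 × 7.85 × 0.32² = 1.6, so 2 per group;
- as printed, SWE-DES (0.2, SD 2.5): 2 × 7.85 × 12.5² ≈ 2,453 per group;
- with the two SDs exchanged, both differences are 0.5 SD. This gives 63 per group (normal) or 64 (t-test), and 64/0.955 = 67.02, rounded up to 68. Here 0.955 is the efficiency of a rank test.

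The figure of 68 is therefore reproduced only with the SDs exchanged. The standardised difference d = 0.5 used below is an assumption resting on that reading. The printed SDs are a separate matter.

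**2. Inputs.**
- Women analysed: 160 × 0.9 = 144, so 72 per group (Sample size estimation, 10% loss).
- Level: 0.025 two-sided, as stated for the primary test; critical value c = 2.2414. The same section closes with "All tests will be two-tailed and conducted at 5% significance level", which conflicts with it; that too is a separate matter.
- ρ, the share of outcome variance lying between centres: not in the document, assumed 0 to 10%.
- Total SD = 1, groups balanced within each centre, attrition not modelled.

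**3. Formulas.** The unstratified test uses variance 2/n for the group difference. Under centre-balanced allocation the true variance is (1 − ρ)·2/n. Hence:

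- size, unstratified = 2Φ(−c/√(1 − ρ));
- power, unstratified = Φ((d/√(2/n) − c)/√(1 − ρ));
- power, within centre = Φ(d/√((1 − ρ)·2/n) − c).

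With n = 72, d/√(2/n) = 0.5/0.1667 = 3.00. The two powers are therefore Φ(0.7586/√(1 − ρ)) and Φ(3.00/√(1 − ρ) − 2.2414).

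**4. Results at 72 per group.**

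| ρ (assumed) | c/√(1 − ρ) | Size, unstratified | Power, unstratified | Power, within centre | Loss (points) |
|---|---|---|---|---|---|
| 0 | 2.241 | 2.50% | 77.6% | 77.6% | 0 |
| 2% | 2.264 | 2.36% | 77.8% | 78.5% | 0.7 |
| 5% | 2.300 | 2.15% | 78.2% | 79.9% | 1.7 |
| 10% | 2.363 | 1.81% | 78.8% | 82.1% | 3.3 |

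**5. Check by simulation.** This used permutation tests at 68 per group, six centres of assumed sizes 40/40/24/16/8/8, blocks of ten, 3,000 null and 1,500 effect replicates. For ρ = 0 / 2 / 5 / 10%:

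- size, unstratified: 3.0 / 2.4 / 2.3 / 1.8%;
- size, within centre: 2.8 / 2.7 / 2.7 / 2.4%;
- power, unstratified: 75.5 / 74.8 / 74.8 / 73.0%;
- power, within centre: 75.3 / 75.5 / 76.5 / 77.2%, so differences of −0.2 / 0.7 / 1.7 / 4.2 points.

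One simulated power has a standard error of √(0.75 × 0.25/1,500) = 1.1 points. At 10% the simulated power levels lie below the formula for 68 per group (76.1 and 79.7%), but the gap between the tests is similar (4.2 against 3.6 points). Direction and order of size are confirmed.

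**The case against.** The strongest objection is that the article never says labels are shuffled across centres. It names the test and the two groups and stops. The permutation scheme is a detail that a journal article may leave to a fuller plan, and that plan may stratify. This stands, so the consequence can be stated only conditionally. What remains is that the article does give the test, analysis set, time point, level, covariate rule and imputation rule, and centre appears in none of them although allocation is built on it.

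Three stronger readings are tempting and are not supported:

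- *That the p-value is conservative as such.* It is so only if outcomes differ between centres (or between blocks over time). If they do not, the size is exactly nominal. The text offers only slight variation in usual care, and nothing in it supports a centre share of 10% or more for self-reported outcomes.
- *That stratifying lifts power from about 77.6% to 82.1%.* That sets the within-centre test at a 10% share against the unstratified test at a zero share. Balanced allocation raises the power of the unstratified test too, to 78.8%, so the like-for-like gain is 3.3 points rather than 4.5.
- *That permuting within centre reproduces the allocation exactly.* In a centre with more than one block it still admits allocations that the blocks of ten ruled out. Only permutation within block follows the scheme fully.

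**Conclusion.** The point holds as a minor one. Centre is used in the allocation, is absent from the primary test as described, and is not reliably picked up by any other stated analysis. If labels are permuted across centres, there is no bias and no excess of false positives. The cost is about 0 to 3 points of power for an assumed centre share of 0 to 10%, with the true size of the nominal 2.5% test between about 2.5 and 1.8%. These figures rest on the assumed share, on d = 0.5 (which needs the two printed SDs exchanged), on 72 women analysed per group and on the 0.025 level. A reader might infer that the primary p-value is invalid; the documents do not support that.

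**What to change.** Before database lock, state that labels in the Fisher test are permuted within centre, and within block where block membership is recorded, with a centre-weighted mean difference as the test statistic. Include centre as a fixed effect in the complementary ANCOVA whenever it is run. If a fuller plan already does this, add it to the public description.

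The cost is a sentence of text and a small change in code. No new data are needed, since the participant code already carries the centre letter. If centres do not differ, essentially no power is lost: 77.6% either way by formula, and 75.5 against 75.3% in the simulation at 68 per group.

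### The six-month primary comparison leaves out the planned T0 scores, and the supportive ANCOVA picks its covariates by baseline significance tests, a criterion that does not identify prognostic variables

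*Protocol article*

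**What the plan says.** The Statistical analyses plan section of the protocol article defines two primary variables, the W-BQ12 and SWE-DES total scores, compared "both at six months after delivery between the two randomized groups using" Fisher's "non-parametric permutation test on the full analysis set (ITT population"), as a "two-sided test on significance level 0.025". It names no baseline score, covariate or stratum for this test.

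Adjustment appears once: "If significant differences in baseline variables are found between the two randomized groups, a complementary analysis of covariance (ANCOVA) will be performed". That model is "adjusted for these baseline variables", meaning those that tested significant. The variables to be tested are not listed.

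The baseline scores are planned data. The Follow-up period and outcome measurement section says that "the primary and secondary outcomes are tested at baseline, early pregnancy (T0), late pregnancy (T1") and at two later visits. The Randomization and allocation concealment section adds that "Randomization is performed before baseline assessment" and that allocation is in blocks of ten within each of six centers. The Blinding section says that participants cannot be blinded.

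**The concern.** The T0 score of the same questionnaire is the obvious candidate predictor of the six-month score, and the plan already collects it. Leaving it out of the primary comparison keeps variance in the error term that a fixed adjustment would remove.

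The conditional rule does not make up for this. Imbalance and prognostic value are different things. A strong predictor that happens to be balanced is left out, and an irrelevant variable that happens to differ is put in. The covariate set is therefore settled by the observed baseline data. At stake are the power of both primary comparisons and the credibility of the one adjusted analysis that the article describes.

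**Working it through.** **1. The plan's own figure.** The Sample size estimation section gives 68 per group for 80% power at 0.05, with a difference of 1.25 and SD 0.40 for W-BQ12, and 0.2 and SD 2.5 for SWE-DES. As printed, these need 2 and 2453 per group (normal approximation), so 68 is not reproduced. With the two SDs exchanged, 1.25/2.5 = 0.5 and 0.2/0.40 = 0.5. A standardized effect of 0.5 needs 63 (normal) or 64 (t-test) per group, or 67 when the t-test figure is divided by 0.955 as an allowance for a rank-type test. The effect of 0.5 used below is therefore an assumption, not a printed value.

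**2. Inputs.**
- d = 0.5 (assumed, from step 1).
- Two-sided alpha 0.025 (Statistical analyses plan).
- n = 72 per group: 160 × 0.9 / 2 (Sample size estimation).
- r, the correlation of the T0 and six-month scores, is not in the article. It is shown from 0.1 to 0.6.

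**3. Power.** ANCOVA on the T0 score multiplies the residual SD by √(1 − r²), so the effective d is 0.5/√(1 − r²). The t-test stands in for the permutation test.

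| r | effective d | power, n = 72, alpha 0.025 |
|---|---|---|
| unadjusted | 0.500 | 76.8% |
| 0.1 | 0.503 | 77.2% |
| 0.2 | 0.510 | 78.6% |
| 0.3 | 0.524 | 80.9% |
| 0.4 | 0.546 | 84.2% |
| 0.5 | 0.577 | 88.3% |
| 0.6 | 0.625 | 93.0% |

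At 68 per group, power is 74.1% unadjusted, 78.4% at r = 0.3 and 86.3% at r = 0.5.

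**4. How often the trigger fires by chance.** With k independent baseline variables tested at 5%, the probability is 1 − 0.95^k: 22.6% for k = 5 and 40.1% for k = 10. Both k and independence are assumptions. With pairwise correlation 0.5, the range is about 18 to 29%. The T0 score itself triggers in about 5% of trials.

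**5. What the trigger recovers.** This was simulated with 68 per group, d = 0.5, one covariate and 40,000 runs per setting. At r = 0.5, adjusting only when the T0 difference has p < 0.05 moves power from 74% to 75%, against 86% when adjustment is always made. In triggered trials the adjusted and unadjusted tests disagree on significance in 21, 33 and 44% of cases at r = 0.3, 0.5 and 0.7.

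**6. Type I error of the primary test.** In the same simulation with no true effect, the unadjusted test rejects in 2.5 to 2.7% of runs at a nominal 2.5%.

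**7. Sensitivity of the remedy to T0 timing.** Suppose there is no true effect, with 72 per group, and knowledge of allocation shifts T0 by an assumed 0.2 to 0.3 SD in one arm. ANCOVA then rejects falsely in about 4 to 8% of trials at r = 0.4 and 9 to 19% at r = 0.6. The unadjusted test stays at about 2.5%.

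**The case against.** An unadjusted permutation test is a legitimate primary analysis, and the plan calls its ANCOVA complementary. That stands, and it rules out several stronger readings.

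- **Two competing primary answers.** A reader might infer that chance decides the primary adjustment. It does not: test, time point, population and alpha are fixed. Chance decides only whether a supportive analysis is added and with which covariates.
- **A badly calibrated primary test.** Given a significant chance imbalance in the T0 score, the unadjusted test's false-positive rate is about 7 to 15% for r = 0.4 to 0.6. That is conditional on an event in about 5% of trials, and in those trials the plan does call for the ANCOVA. Overall the test holds 2.5%.
- **The power shortfall as a result of this choice.** At 72 per group and alpha 0.05, unadjusted power would be 84.6%. The drop to 76.8% comes from sizing at 0.05 and testing at 0.025, which is a separate matter.
- **A T0 score for every woman.** The article plans questionnaires with reminders. Its full analysis set requires one follow-up measurement, not a T0 score.

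Two further points limit the argument. T0 is early pregnancy and the endpoint is six months after birth, so a low r is plausible. At r = 0.1 to 0.2 the gain is under two points. And since randomization precedes an unblinded T0, a T0 difference could reflect knowledge of allocation as well as chance. The article shows no evidence of such a shift, but adjustment would be exposed to it and the unadjusted test is not.

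**Conclusion.** The point holds as a matter of efficiency and pre-specification, not of validity. The plan leaves out a planned baseline measure from both primary comparisons, and it lets significance tests choose the covariates of its only adjusted analysis. The loss ranges from negligible at r = 0.1 (76.8 against 77.2%) through about 4 points at r = 0.3 to about 16 points at r = 0.6. All of these rest on d = 0.5, 72 per group, alpha 0.025 and a T0 score unaffected by allocation. Under those assumptions, adjustment brings power back above 80% from r of about 0.3. The trigger recovers almost none of this. The change is worth making while recruitment continues, but the results would not be invalid without it.

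**What to change.** - Delete the baseline-significance trigger.
- Before database lock, pre-specify for both outcomes an analysis of the six-month score on arm, the T0 score of the same instrument, and centre (the randomization stratum). A permutation p-value can be used if a non-parametric test is wanted.
- For women still to be enrolled, have the T0 questionnaire completed before allocation is revealed.
- Always report the unadjusted Fisher permutation test beside the adjusted result.

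The analysis change costs plan wording and a few lines of code and needs no new measurements. Moving T0 ahead of disclosure also needs a change of procedure at the centers, because baseline questionnaires now travel in the randomization envelope. The remaining downside is small: for women already enrolled, the adjusted result relies on T0 being unaffected by knowledge of allocation, and the unadjusted test is the check on that.
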